### Monitoring

The study procedure will be performed according to the manufacturer’s protocol. We do not intend to change the study protocol after recruiting the first patient. If some circumstances that influence the research conditions occur, the changes will be noted at ClinicalTrials.gov (the protocol registry site), and the Bioethics committee will be notified. An independent data and safety monitoring board (DSMB) will be established before the beginning of the study. The DSMB will review the data after the recruitment of 25%, 50%, and 75% of participants to evaluate the study progress and adverse events.

### Statistical analysis

Descriptive statistics will be calculated to characterize and present the study population and baseline findings. Data normality distribution will be verified using the Shapiro-Wilk test. For normally distributed continuous variables, comparative analyses will be performed using Student’s *t-*test. Continuous variables that are not normally distributed will be compared using the Mann-Whitney *U* test. Group comparisons for nominal variables will be conducted using the Fisher exact test or the *χ*^2^ test, as deemed appropriate. Linear regression analysis with the baseline value of the outcome as a covariate will be used to compare the treatment groups. Log transformation will be performed in case of apparent violation of the normal distribution of the data. All tests will be two-tailed, and differences will be considered significant at the level of *p* ≤ 0.05. The number of missing data points will be presented for each variable. Nominal variables will be presented as *n* (% of the group). The outcomes will be presented as differences in medians for continuous data with non-normal distribution and as differences in means for data with normal distribution, both with a 95% confidence interval.

The clinical inference will be based on 95% confidence intervals for the regression coefficient for treatment effect. If the 95% confidence interval does not include 0, we will conclude that the difference between the treatment groups is clinically significant.

Data from the CBGM and CGM will be analyzed separately. To evaluate the capillary blood glucose levels at 30, 60, 90, 120, 150, and 180 min after the administration of the prandial bolus and the number of hypoglycemia episodes, data from the CBGM will be used. Data from CGM will be adopted to calculate the GR, PG, time to PG, MAGE, and time in the postprandial glucose range between 70 and 180 mg/dl (4.0–10.0 mmol/l).

The AUC will be calculated geometrically by applying the trapezoid rule. The incremental area under the blood glucose response curve (iAUC) is defined as the sum of all sensor excursions from the baseline value for the 3-h post-meal period. The positive AUC (pAUC) will be calculated based on the intersection points of the estimated curve with the baseline and integration of the area above the baseline.

Intention-to-treat analysis will be performed as a primary approach. Additionally, the data of participants who will finish the study according to the protocol (per-protocol) will be used as a sensitivity analysis.

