## Methods

### Trial design

This study was designed as a randomized, double-blind, crossover study with an allocation ratio of 1:1. The trial was registered at ClinicalTrials.gov (NCT04019821) before the inclusion of the first patient. Any important changes in the protocol are introduced.

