### Intervention

The intervention will involve the administration of insulin for an h-GI breakfast in the form of Super Bolus. The participants will eat a h-GI breakfast for the two following days and receive a prandial insulin bolus in the form of a Super Bolus 1 day and a Normal Bolus the next day. The h-GI breakfast consists of breakfast cereal, cornflakes with added cold milk: 50 g CHO will come from the cornflakes and 10 g of CHO from the 2% milk (200 ml). Super Bolus is defined as the 50% increase in prandial insulin dose compared with the dose calculated based on the individual patient’s insulin-carbohydrate ratio (ICR) and the simultaneous suspension of basal insulin for 2 h. The definition of Super Bolus is based on the patients’ best experiences. Normal Bolus will be defined as the prandial insulin dose calculated based on the individual’s ICR.

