### Sample size

The sample size was estimated based on the calculations performed using the StatsDirect statistical software (V.3.1.4, StatsDirect, Chesire, UK). A total of 72 participants will be required to show a difference of 30 mg/dl (1.7 mmol//l) and an SD of 41 (which corresponds to the standard deviation of the paired differences being 82) and standard deviations for observations within treatment being 58 at the 90th minute of the study (the primary endpoint), with *α* = 0.05 and 80% power—assuming a 20% withdrawal rate. The correlation was set to 0 (conservative approach). We assume that glycemia differences between the study groups mentioned above are significant for metabolic control.

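### The analysis section names no within-participant method for a crossover trial sized on paired differences; followed as written, its 95% CI is miscalibrated, most likely too wide

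*Protocol article*

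**What the plan says.** The Trial design section states: "This study was designed as a randomized, double-blind, crossover study with an allocation ratio of 1:1". Under Intervention, participants "receive a prandial insulin bolus in the form of a Super Bolus 1 day and a Normal Bolus the next day", so each child supplies one observation per bolus on separate days. The Study procedure section confirms that both sequences give both boluses.

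The Sample size section is built on this pairing. It targets 30 mg/dl at 90 minutes and cites "the standard deviation of the paired differences being 82", with a within-treatment SD of 58 and a correlation of 0 that it labels conservative.

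The Statistical analysis section then sets out:

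- for inference: "Linear regression analysis with the baseline value of the outcome as a covariate will be used to compare the treatment groups", with conclusions drawn from whether the 95% CI of the treatment coefficient includes 0;
- for normal data, Student's t-test, with no statement of paired or unpaired;
- for other continuous data: "Continuous variables that are not normally distributed will be compared using the Mann-Whitney" U test;
- for nominal data: "Group comparisons for nominal variables will be conducted using the Fisher exact test or the" chi-square test.

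Nowhere does the article mention a participant effect, a period or sequence term, a mixed model, a paired t-test, a signed-rank test or a McNemar test.

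**The concern.** The design and the sample size treat the child as his or her own control; the analysis section does not. A regression on treatment and baseline alone treats a child's two readings as unrelated. Its standard error then contains the between-child variation that a crossover is meant to remove, and any shift between the two test days also goes into the error.

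This is more than detail left to an analysis plan. The article itself fixes the model's only stated covariate, names the tests and sets the decision rule. An analyst who followed it literally would report an interval that does not have its stated coverage and would lose precision on every endpoint.

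**Working it through.** **Inputs from the Sample size section:** difference 30 mg/dl; SD within treatment 58; SD of paired differences 82; SD 41; correlation 0; 80% power; 20% withdrawal; N = 72. The tests are two-sided at 0.05.

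**Consistency of the SDs.** With correlation 0, the SD of a paired difference is 58 × √2 = 82.0, and half of 82 is 41. The figures agree and describe a paired structure.

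**Reproducing 72.** Comparing half period-differences between the two sequences:

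n per sequence = 2 × (1.960 + 0.842)² × 41² / 30² = 29.3, rounded up to 30.

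That is 60 in total, and 60 × 1.2 = 72 (dividing by 0.8 would give 75). The paired form, ((1.960 + 0.842) × 82 / 30)² = 58.6, gives 59. So 72 follows from a within-child analysis.

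**Effect of ignoring the pairing.** Completers: 72 × 0.8 = 57.6, taken as n = 58. Let r be the within-child correlation.

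- SE from the analysis that ignores pairing: 58 × √(2/58) = 10.77 mg/dl, whatever r is.
- True SE of the treatment difference: 58 × √(2(1 − r)/58) = 10.77 × √(1 − r).
- Actual type I error of the analysis that ignores pairing: 2 × [1 − Φ(1.96/√(1 − r))].
- Its power: Φ((30 − 1.96 × 10.77) / true SE).
- Power of the paired analysis: Φ(30 / true SE − 1.96).

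| r | True SE | Half-width, ignoring pairing | Half-width, paired | Type I error, ignoring pairing | Power, ignoring pairing | Power, paired |
|---|---|---|---|---|---|---|
| −0.2 | 11.80 | 21.1 | 23.1 | 7.4% | 77% | 72% |
| 0 | 10.77 | 21.1 | 21.1 | 5.0% | 80% | 80% |
| 0.3 | 9.01 | 21.1 | 17.7 | 1.9% | 84% | 92% |
| 0.5 | 7.62 | 21.1 | 14.9 | 0.6% | 88% | 98% |
| 0.7 | 5.90 | 21.1 | 11.6 | 0.03% | 93% | 99.9% |

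Only r = 0 comes from the document; the other values are assumptions shown as a range. At r = 0.5 the reported SE is 10.77/7.62 = 1.41 times the true one.

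**Simulation check.** Each cell had 4,000 trials of 58 children, with an assumed baseline SD of 15, an assumed baseline slope of 0.3 and no period effect. Regression with the baseline covariate and no pairing had type I error 5.1%, 2.0%, 0.8% and 0.03% at r = 0, 0.3, 0.5 and 0.7. Regression of within-child differences stayed between 4.7% and 5.5%. Power at r = 0.3 and 0.5 was 82% and 87% ignoring pairing, against 90% and 97% paired. Baseline adjustment therefore does not replace the pairing in this setting.

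**The case against.** The text does not say unpaired t-test, ordinary regression or 144 independent records. These are inferences from the missing participant term and from the pairing of Student's t with Mann-Whitney U rather than the signed-rank test. That stands, and the point is worded accordingly.

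The named tests can also be valid in a crossover. A t or Mann-Whitney test may compare within-child period differences between sequences, and Fisher or chi-square may be applied to sequence by direction of discordance. The sample size fits such a comparison (SD 41, 30 per sequence), and the article does call the sequences groups. But the analysis section does not describe this use, and its wording about treatment groups reads more naturally as bolus type. What remains is an unspecified unit of analysis that reads as unpaired, not tests that are invalid in themselves.

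The planning correlation of 0, at which the two analyses coincide, might seem to justify ignoring the pairing. It is labelled a conservative planning choice, not an expected value.

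Four stronger readings are tempting, and the documents do not support them:

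- **False precision.** A reader might infer that counting each child twice makes the result too significant. For positive correlation the opposite holds.
- **Hypoglycemia tested with Fisher.** The endpoint is a number of episodes, and Fisher or chi-square is assigned only to nominal variables. No test is explicitly assigned to hypoglycemia, and power figures for it would rest on assumed event rates.
- **Competing routes to the primary conclusion.** The section makes the regression interval decisive.
- **A failed sample size.** Ignoring the pairing still gives about 80% power or more for any non-negative correlation shown.

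**Conclusion.** The contradiction is real and sits in the primary inferential model: a crossover sized on paired differences has an analysis section with no within-participant element. Followed as written, the 95% CI and p-value are miscalibrated unless the within-child correlation is 0. For an assumed correlation of 0.3 to 0.5, the interval's half-width is about 3 to 6 mg/dl too large (21.1 against 17.7 and 14.9), and 8 to 10 percentage points of power are lost.

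The expected damage is lost precision and an interval without its stated coverage, not a false-positive result. Type I error would be inflated only by a negative correlation (7.4% at −0.2). The lack of bias depends on complete, balanced pairs. With 20% withdrawal assumed and intention-to-treat as the primary approach, some children may contribute one day only; without a period term, day and treatment effects could then mix.

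The sizes rest on SD 58, 58 completers and the assumed correlations.

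**What to change.** Make the primary analysis of 90-minute glucose a within-participant model. Either of these will do:

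- a linear mixed model with treatment, period, period-specific 0-minute glucose and a random participant effect; or
- the equivalent regression on within-child differences with a period term.

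Report the treatment difference with its 95% CI, and use the same model for the other continuous endpoints.

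For non-parametric checks, use the signed-rank test or Hodges-Lehmann estimate on within-child differences, or state explicitly that Mann-Whitney compares period differences between sequences. For hypoglycemia, name a paired method: McNemar or conditional/mixed logistic regression for any episode, and a paired count model for the number of episodes. A fixed sequence term and dropping the Shapiro-Wilk step are optional.

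N stays 72 and no new data are needed. The cost is rewording the analysis section and any analysis plan, preferably before unblinding. Recruitment began in January 2020, so the registry entry and bioethics committee notification described under Monitoring also apply.

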The calculation of insulin doses will be performed based on the individual’s ICR counted per 10 g of CHO. The normal bolus will be calculated as 6 × ICR, and the Super Bolus will be calculated as 150% × 6 × ICR, with the suspension of basal insulin for 2 h after the delivered prandial bolus. The CRF containing the protocol for both groups, the personal data, and the calculations concerning insulin doses will be filled in for both groups on the first day. A closed envelope with patient allocation will be attached to the CRF. In the next 2 days, patients will eat h-GI breakfast, and the bolus order will depend on the allocation group. Nurses who will not be involved in the study will administer the right type of bolus. To ensure that the study protocols will not be mixed up and remain blind, the nurse administering the premeal bolus will check the allocation in the envelope and will provide the appropriate type of bolus. The study duration per day is planned for 3 h. No additional meals, snacks, or correction boluses are allowed during this time. An observation time of 3 h is defined as an approximation of the total lasting hypoglycemic effect after a subcutaneous insulin bolus dose. The capillary blood glucose level will be measured with a Contour® Plus Link Meter at 0, 30, 60, 90, 120, 150, and 180 min after insulin administration with a continuously working monitoring system. There is a high possibility that rapid glycemic fluctuations will be observed after an h-GI meal. Therefore, the blood glucose level can be checked with both the CGM and glucometer to obtain the highest accuracy of glycemic level at the specified time point. Caregivers and patients will also be instructed to report symptoms of hypoglycemia with additional glycemia measurements. Hypoglycemia will be defined as the glucose level below or equal to 70 mg/dl (≤ 3.9 mmol/l), which is treated as a clinical hypoglycemia alert according to the ISPAD Guidelines 2018.^1^ If hypoglycemia occurs, the patient will receive 0.3 g/kg of glucose/saccharose. After 15 min, the glucose level must be controlled again. If hypoglycemia persists, the patient will receive the next dose of glucose/saccharose, until a glucose level over 70 mg/dl is achieved. The presence of hypoglycemia will not suspend the study process, and SMBG will be performed as it is established. The records from the CGM will be registered using the Medtronic Care Link Pro Software and discussed with the patients for educational purposes. The participants may discontinue the trial at any point in time without giving a reason. The researchers will make every effort to supervise, educate, and regularly control the patients to provide the proper study process.

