
### End points

The following is the primary endpoint:
Capillary blood glucose level 90 min after the administration of the prandial bolus as meals with h-GI typically cause blood glucose level peak within 60–90 min in T1D patients

The following are the secondary endpoints:
Capillary blood glucose levels at 30, 60, 120, 150, and 180 min after administration of the prandial bolusThe number of hypoglycemia episodes based on SMBG

The following data are based on the CGM:
Glycemic rise (GR)—the difference between the baseline and the maximum glucose valuePeak glucose level (PG)—the maximum value of glycemia during 3 h of post-mealtimeTime to PGArea under the blood glucose curve (AUC)Mean amplitude of glycemic excursion (MAGE)—the standard deviation of blood glucose (SDBG) obtained from all blood glucose concentrations within 3 h of post-meal timeTime in the postprandial glucose range between 70 and 180 mg/dl (4.0–10.0 mmol/l)

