Adjustment of the type and dose of insulin for h-GI meals remains a challenge. According to Dżygało et al., neither of the two insulin analogs, glulisine nor aspart, provide a stabilized glycemic profile after an h-GI meal [28]. The new formulation of faster-acting insulin aspart (faster aspart) has a more rapid onset of appearance and greater early exposure in comparison with aspart for children and adolescents. Using this new formulation, a statistically significant reduction of 2 h for postprandial glycemia after a standardized meal was reported [29, 30]. However, due to regulatory approval and availability, its common use in clinical practice is limited. Lujif et al. demonstrated that the administration of prandial rapid-acting insulin analogs 15 min (instead of 30 min) before a meal, directly at the start of eating, resulted in a lower rate of PPH without an increased risk of hypoglycemia [21]. Therefore, we decided to deliver an insulin bolus 15 min before a meal. O’Connel et al. tested two types of prandial bolus for an h-GI meal: a normal bolus (given over 3 min before the meal) vs dual (50:50% over 2 h) and found no difference between them [10]. Regardless of the bolus type, high glycemic excursions were still observed, with a mean glycemic rise of + 95.4 mg/dl compared to the baseline [10]. An additional dose of insulin was also considered as a possible solution for the h-GI meals issue. Groele et al. compared the dose of prandial insulin calculated based on the individual patient’s ICR with the dose increased by about 30% for an h-GI meal and concluded that the frequencies of PPH and hypoglycemia were similar in both groups, but the additional dose of insulin significantly reduced glucose excursion in terms of the mean postprandial glycemia (47.4 ± 39.8 mg/dl vs 76.2 ± 58.2 mg/dl) [22]. We know that a dose of insulin increased by 30% does not cause a higher incidence of hypoglycemia episodes and leads to lower postprandial glycemia, but the incidence of hyperglycemia episodes still remains unsatisfactory. Therefore, we decided to conduct this study based on the Super Bolus idea to achieve a reduction in the frequency of PPH, with a simultaneous decrement in glycemic rise and hypoglycemia episodes. The available pertinent literature only refers to in-silico studies and clinical practice [23, 24]. We defined a Super Bolus as a boost of prandial insulin (increased by 50% in comparison with the dose calculated based on individualized patient’s ICR) and a simultaneous suspension of the basal insulin for 2 h. During that time, the insulin is still acting, and 2 h seems to be a short period for a rebound effect. Moreover, our patients reported the best experience with the above-mentioned combination.

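### The hypoglycemia episode count has no suitable analysis: if lows are sparse, the median, log and baseline-adjusted regression rules fail on it, and the tests that still work ignore the crossover pairing

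*Protocol article*

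**What the plan says.** End points lists the "number of hypoglycemia episodes based on SMBG" as a secondary endpoint. Study procedure sets the threshold ("Hypoglycemia will be defined as the glucose level below or equal to 70 mg/dl") and the window ("The study duration per day is planned for 3 h"). Statistical analysis names the meter as the data source: for the timed glucose values and "the number of hypoglycemia episodes, data from the CBGM will be used".

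Statistical analysis then recognises two kinds of variable.

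- **Continuous.** A Shapiro-Wilk check is followed by Student's t-test if normal. Otherwise: "Continuous variables that are not normally distributed will be compared using the Mann-Whitney" U test. On reporting: "The outcomes will be presented as differences in medians for continuous data with non-normal distribution", with means used for normal data and a 95% confidence interval for both. On transformation: "Log transformation will be performed in case of apparent violation of the normal distribution of the data".
- **Nominal.** Fisher's exact or chi-square test, presented as n and percent.

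Treatments are compared by linear regression adjusted for the outcome's baseline value, and inference rests on the 95% confidence interval of the treatment coefficient. The section does not say which class the episode count belongs to, and it defines no any/none version of it.

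Hypoglycemia is part of the aim. Background sets out to learn whether the Super Bolus helps avoid late hypoglycemia, and the Discussion looks for a lower frequency of postprandial hyperglycemia "with a simultaneous decrement in glycemic rise and hypoglycemia episodes".

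**The concern.** A count of lows over 3 h on one morning is a small whole number, and it may well be 0 for most children. A difference in medians, a log transformation and a regression on the outcome's own baseline value are workable for glucose in mg/dl. They do not carry over to such a count.

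At stake is how half of the trial's question is reported. A median difference of 0 printed for hypoglycemia could be taken as evidence that the two boluses are equally safe, when it only says that fewer than half of the test days under each bolus had a low. If the trial team departs from the rule once the data are in, the effect measure for hypoglycemia will have been chosen after the fact.

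**Working it through.** **Inputs.** From Sample size: 72 children and 20% withdrawal, so 72 × 0.8 = 57.6, about 58 completers. From Study procedure: one 3 h window per treatment. Assumed, because no hypoglycemia rate is given: 5% to 25% of Normal Bolus test days with at least one low, tripled under the Super Bolus.

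**The plan's own figure.** The sample size concerns glucose at 90 min, not hypoglycemia. It reproduces closely: ((1.960 + 0.842) × 82 / 30)² = 58.6, so 59 completers. Allowing for 20% withdrawal gives 59 / 0.8 = 74 or 59 × 1.2 = 71, against the stated 72. About 58 completers is therefore a fair basis.

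**Median rule.** With 58 values, a treatment's sample median can exceed 0 only if at least 29 children have a low. From Binomial(58, p), P(X ≥ 29) is:

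| Share of test days with a low | P(median > 0) |
|---|---|
| 20% | 3 × 10⁻⁷ |
| 30% | 0.001 |
| 40% | 0.079 |

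Share of simulated trials (Poisson counts, 58 per condition, 2,000 runs, independent days) in which the difference in medians is exactly 0 although the share of days with a low triples:

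| Normal → Super Bolus | Median difference = 0 |
|---|---|
| 5% → 15% | 100% |
| 10% → 30% | 99.95% |
| 13% → 39% | 94% |
| 15% → 45% | 73% |
| 16.7% → 50% | 46% |
| 20% → 60% | 5% |
| 25% → 75% | 0% |

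The turning point is where the higher rate reaches one half: 3p = 1/2, so p = 1/6.

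**Log rule.** Suppose 6 of 60 children have a low under one bolus and 18 of 60 under the other. Zeros then make up (120 − 24) / 120 = 80% of observations. Their logarithm does not exist, and no offset is stated.

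**Regression rule.** The covariate is the outcome's baseline value. Episodes are counted after the bolus, so the count has no baseline counterpart.

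**What still works.** In the 6 versus 18 of 60 example, the difference in medians is 0, but Mann-Whitney gives p = 0.006, Fisher p = 0.011, and untransformed, unadjusted regression a mean difference of 0.20 (95% CI 0.06 to 0.34). Simulated power with 58 completers:

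| Method | 5% vs 15% | 10% vs 30% |
|---|---|---|
| Mann-Whitney | 46% | 81% |
| Fisher | 32% | 73% |
| Untransformed regression | 46% | 82% |

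All three treat the two days of one child as independent.

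**Paired alternative.** For 10% versus 30% and 58 children, exact McNemar has about 72% power when days are independent, the same as Fisher to within a point. If a child's two days are correlated on a latent normal scale, McNemar rises to about 77–79% at a correlation of 0.3 and 87% at 0.6, while Fisher stays at 72–75%.

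As an example of the output, take the same 6 versus 18 of 60 with 4 children low on both days. The discordant pairs are then 2 and 14, and the paired risk difference is (14 − 2) / 60 = 0.20. Its standard error is √(16 − 12²/60) / 60 = 0.061, so the 95% CI is 0.08 to 0.32.

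**The case against.** A reader might infer that the trial would show no difference in hypoglycemia even if lows tripled. The documents do not support that. The zero belongs to the median summary alone. The listed Mann-Whitney test, Fisher's test on any versus none, and an untransformed regression would all react to a tripling, as the power figures show.

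Three further points stand.

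- The medians sentence is worded for continuous data. It reaches an episode count only by default, and the nominal route is also open.
- That most counts are zero is an assumption. From a Normal Bolus rate of about 20% upward, a tripling would give a non-zero median difference.
- Lows are not visible through this summary alone. Harms are to be reported under the CONSORT harms extension, and the DSMB reviews adverse events at 25%, 50% and 75% of recruitment.

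It can also be said that the effect measure for one secondary endpoint is commonly left to an analysis plan that is not shown. That carries less weight here. The article does not stay silent: it names this count among the outcomes to be evaluated and states general transformation, effect-measure and regression rules, none of which suits it. Mann-Whitney supplies a p-value without a usable effect size, so a significant p-value could stand beside a median difference of 0. Reaching the untransformed regression means setting aside both the log rule and the baseline covariate. Harms reporting and DSMB review do not fix a treatment comparison.

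**Conclusion.** The point holds as a defect in how one endpoint is to be analysed and reported. It does not mean that a large difference would go undetected. Each listed route for the episode count gives a degenerate effect measure, needs an input that does not exist, or uses an unpaired test in a crossover.

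The median difference is uninformative if fewer than half of test days have a low under both boluses; under a tripling, that means a Normal Bolus rate below about 1/6. This is plausible for a 3 h window, but the documents do not state it. The failure of the log at zero and the missing baseline value do not depend on the rate, beyond some zeros occurring.

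The gain in power from pairing is nil if a child's two days are independent. At 10% versus 30% it is roughly 5 to 12 percentage points for latent correlations of 0.3 to 0.6, which are also assumed. The firmer gain is an interpretable effect with a valid interval for an outcome that carries part of the stated aim.

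**What to change.** In Statistical analysis, exempt the hypoglycemia endpoint from the median, log-transformation and baseline-adjusted regression rules. State that any hypoglycemia (yes/no) per test period will be compared within child by exact McNemar test, with the paired risk difference and its 95% CI. Conditional logistic regression with an odds ratio is an acceptable alternative. Report the mean number of episodes per test day by treatment as support.

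The cost is one or two sentences and no new data. The any/none measure drops information on repeat episodes; the supporting mean keeps it.

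### The decision rule equates a 95% confidence interval that excludes 0 with clinical significance and makes no use of the 30 mg/dl on which the trial was sized

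*Protocol article*

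**What the plan says.** The protocol article, Statistical analysis, states the basis for its conclusions: "The clinical inference will be based on 95% confidence intervals for the regression coefficient for treatment effect". The next sentence gives the rule: "If the 95% confidence interval does not include 0, we will conclude that the difference between the treatment groups is clinically significant". The same section separately sets two-tailed testing at p ≤ 0.05. Neither sentence mentions a size of effect, a direction or a particular endpoint.

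The Sample size section is the only place that says how large a difference matters. It begins "A total of 72 participants will be required to show a difference of 30 mg/dl", refers to the 90-minute primary endpoint, and closes: "We assume that glycemia differences between the study groups mentioned above are significant for metabolic control".

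**The concern.** A 95% interval that excludes 0 carries the same information as a two-sided p-value below 0.05 from the same model. The section already has that criterion, so the rule adds nothing except the word clinical. Meanwhile the one figure that the article ties to metabolic control, 30 mg/dl, plays no part in the conclusion.

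At stake is the wording of the trial's main claim. The Discussion expects the results to feed into recommendations on the Super Bolus. Under the rule, an estimate clearly smaller than the planned 30 mg/dl would be reported as clinically significant without any argument about its size. The End points section lists many secondary measures (five further time points, hypoglycemia episodes, glycemic rise, peak, time to peak, AUC, MAGE, time in range). None has a stated relevant difference, and nothing in the rule keeps it from being applied to them.

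**Working it through.** **Inputs (protocol article, Sample size).**
- Target difference: 30 mg/dl.
- SD of paired differences: "which corresponds to the standard deviation of the paired differences being 82".
- SD within treatment: "standard deviations for observations within treatment being 58 at the 90th minute of the study".
- Correlation: "The correlation was set to 0 (conservative approach").
- Alpha, power and withdrawal: "0.05 and 80% power—assuming a 20% withdrawal rate".

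The two SDs agree with each other: 58 × √2 = 82.0 at correlation 0.

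**Reproducing the planned size.** With the paired normal approximation, n = ((1.960 + 0.842) × 82 / 30)² = 58.6, so 59 completers. Allowing for withdrawal gives 59 / 0.8 = 73.75, so 74, or 59 × 1.2 = 70.8, so 71. Sixty completers × 1.2 gives exactly 72. The stated 72 is therefore consistent with these inputs, and the SD of 82 is the right one to use below.

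**Smallest observed difference that the rule calls clinically significant.** For an unadjusted paired analysis this is t(0.975, n − 1) × SD / √n. If 20% of 72 withdraw, 72 × 0.8 = 57.6, about 58, complete.

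| Completers | SD of differences | Calculation | Threshold (mg/dl) | Interval at threshold | Share of 30 |
|---|---|---|---|---|---|
| 58 | 82 (plan, correlation 0) | 2.002 × 82 / √58 | 21.6 | 0 to 43.1 | 72% |
| 72 | 82 (plan, correlation 0) | 1.994 × 82 / √72 | 19.3 | 0 to 38.5 | 64% |
| 58 | 58 (correlation 0.5, assumed) | 2.002 × 58 / √58 | 15.3 | 0 to 30.5 | 51% |
| 72 | 58 (correlation 0.5, assumed) | 1.994 × 58 / √72 | 13.6 | 0 to 27.3 | 45% |

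The correlation of 0.5 is my assumption, not a value from the article. It gives SD = 58 × √(2 × (1 − 0.5)) = 58. I show it because the article itself calls correlation 0 conservative. In the last row, a result at the threshold is called clinically significant although its whole interval lies below 30 mg/dl.

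**Chance of the label when the true difference is 15 mg/dl.** This comes from the non-central t distribution with n − 1 degrees of freedom and non-centrality 15 / (SD / √n).
- SD 82: 0.28 with 58 completers (non-centrality 1.39) and 0.33 with 72 (1.55).
- SD 58 (assumed correlation 0.5): 0.49 with 58 completers and 0.58 with 72.

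**The case against.** The strongest reply is that this is one word in one sentence. The estimate, its interval, the test and the sample size all stay as they are. The article promises differences with 95% confidence intervals, so any reader can make the comparison with 30 mg/dl. This is right about severity: the defect does not touch the trial's validity. It does not rescue the rule, because nothing elsewhere in the article corrects it. Nor is the point a detail left to an unseen analysis plan, since the article itself fixes the rule.

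Four stronger readings are tempting, and the document does not support them.

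- **That 30 mg/dl is a declared minimum, so anything smaller is trivial.** The Sample size section calls differences of that size significant for metabolic control. It does not say that smaller ones are irrelevant. The rule is faulty because it asserts clinical significance with no reference to size, not because 20 mg/dl is known to be unimportant.
- **That the rule is stated to cover every endpoint.** It speaks of the regression coefficient for treatment and neither limits nor extends itself. The accurate statement is that it is not limited to the primary endpoint.
- **That the trial would declare the Super Bolus clinically beneficial.** The rule labels a difference, without direction. Hypoglycemia is a separate endpoint and harms are reported separately.
- **That clinical relevance should require the whole interval to lie beyond 30 mg/dl.** With SD 82 that needs an observed 30 + 21.6 = 51.6 mg/dl (58 completers) or 30 + 19.3 = 49.3 (72 completers). If the true effect were exactly 30, it would happen about 2.5% of the time. The trial was powered to exclude 0, not 30.

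**Conclusion.** The rule is wrong as written and should be fixed, though it is not a fatal flaw. It presents statistical significance as clinical significance, leaves out the only difference that the article links to metabolic control, and is not confined to the 90-minute endpoint. On the plan's own inputs, the label is earned from about two thirds to three quarters of the planning difference.

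The thresholds rest on an unadjusted paired analysis with correlation 0. The planned adjustment for baseline, or a positive within-child correlation, would lower them; the correlation-0.5 rows illustrate the latter and are only as good as that assumption. The core of the point does not depend on these figures: an interval excluding 0 contains no judgement of size at any SD.

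**What to change.** Replace the sentence in the Statistical analysis section with wording such as:

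> If the 95% CI excludes 0, the difference is statistically significant; clinical relevance at 90 min will be judged by comparing the point estimate and its 95% CI with the pre-stated 30 mg/dl.

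Add that no automatic statement of clinical significance will be made for secondary endpoints.

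The comparison should use the estimate and the interval together, not a cut-off on the estimate alone. With 58 completers and SD 82, an estimate of 22 mg/dl has an interval of 22 ± 21.6, about 0.4 to 43.6. That result remains compatible with 30 and should not be dismissed as falling short of it. A cut-off of 30 on the estimate would also be missed about half the time when the true effect is exactly 30.

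The cost is one sentence of text. Type I error, power, sample size, conduct and data collection are unchanged. The real price is that clinical significance becomes harder to claim and must be argued from the size of the effect.
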